## **9. Analysis plan**

In our primary analyses, we will multiple imputation for missing data and use linear mixed effects models to compare the change in mean daily step count from baseline to 12-week intervention period, adjusting for baseline step count and time. To test of the robustness of our findings we will also evaluate models using collected data without imputation. All hypothesis tests will be two-sided using a two-sided alpha of 0.05 as our threshold for statistical significance. In secondary analyses, we will evaluate how differences in inpatient and changes in post-discharge step counts are associated with secondary outcome measures.

In exploratory analyses, we will compare how differences in hospital mobility protocols are associated with differences in step counts. We will also conduct a qualitative analysis to evaluate participant perceptions of the intervention.

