### *5.4 Accrual*

We will aim to enroll and randomize 300 patients. We estimate that a sample size of at least 300 participants (150 per arm) will provide 90% power to detect a difference of 700 steps in the change in mean daily step count from baseline to the intervention period between intervention and control, using a 2-sided  $\alpha$  of 0.05, assuming a baseline mean step count of 5000 steps in the control group with a standard deviation of 2500 steps, and accounting for a 10% dropout rate.

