## *8.2 Procedures*

Each day, the research coordinator will use an electronic health record query to generate a list of patients that are admitted to medicine and oncology floors and meet AMPAC and age requirements. At enrollment, the research coordinator will administer two additional screening questions to determine eligibility (owns a smart phone and not in another physical activity study) via the RedCap portal. If the participant successfully passes the screening questions, the patient can be consented to the study. The research coordinator will next present a series of to the patient to be completed through the Way to Health portal. These instruments include: the Pittsburgh Sleep Quality Index, Karolinska Scale, Activity of Daily Living-Instrumental Activities of Daily Living Survey, Life Space Activity Survey, Mini-Nutritional Assessment Survey, Edmonton Symptom Assessment Survey, Treatment Burden Questionnaire, Lubben Social Network Scale, Self Rated Health Survey, and Dementia Tool.

After completing the enrollment assessment, the research coordinator will show patients how to use the wearable device which can be worn on wrist (like a watch), carried in any pocket, or clipped to hospital gown. After they are enrolled, participants will receive a daily text message

with a link to complete two surveys in Way to Health about their sleep quality and symptom assessment for up to 10 days of hospital admission, or until they are discharged.

Upon hospital discharge, there will be a one-week run-in period after discharge to estimate baseline step counts for all patients. After week 1, all participants will be notified to complete post-discharge baseline surveys. For all patients with a baseline step count, they will be randomly assigned to control or intervention using block sizes of two and stratifying on baseline step count (<5000 daily steps, 5001 to 7500, or > 7500) and hospital admission floor.

Participants in the control group will continue to have data collected passively. Participants in the control arm will only receive study communications when it is time for them to complete surveys in the Way to Health system.

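### Admission floor is a randomisation stratum but is not in the primary model's stated adjustment set; if floor is prognostic, the standard error is slightly too large

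*Protocol*

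**What the plan says.** Protocol section 8.2 (Procedures) randomises patients who have a baseline step count "using block sizes of two and stratifying on baseline step count (<5000 daily steps, 5001 to 7500, or > 7500) and hospital admission floor". Two factors therefore define the strata.

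Protocol section 9 (Analysis plan) will "use linear mixed effects models to compare the change in mean daily step count from baseline to 12-week intervention period". The covariates of that model are then listed: "adjusting for baseline step count and time". Baseline step count is in that list; admission floor is not, and no other section adds it. The random-effect structure of the mixed model is not stated. Section 9 mentions differences between floors only indirectly, through an exploratory comparison of step counts by hospital mobility protocol.

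The test level is fixed in the same section: "All hypothesis tests will be two-sided using a two-sided alpha of 0.05 as our threshold for statistical significance".

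**The concern.** Stratified blocks force the arms to be nearly balanced on floor. That balance removes between-floor variation from the true sampling variance of the arm difference. A model without floor does not know this: it leaves the between-floor variation in the residual and reports a standard error that reflects it. The interval is then wider than it needs to be, and the test rejects less often than its nominal 5% under the null.

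There is some reason to think floor could matter. The floors are medicine or oncology floors (section 5.3), which hold different kinds of patient, and the sponsor chose floor as a stratifier. What is at stake is a little precision in the primary comparison, and agreement between how the trial randomises and how it analyses.

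**Working it through.** **1. Design against analysis.**
- Strata (section 8.2): baseline step category (three levels) × admission floor, blocks of two.
- Adjustment set (section 9): baseline step count, time.
- Left over: admission floor.

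**2. Inputs.**
- Section 5.4: 150 per arm, 10% dropout, so 150 × 0.9 = 135 completers per arm; target difference 700 steps; two-sided alpha 0.05; 90% power.
- SD: section 5.4 gives 2500, but attaches it to the baseline count ("assuming a baseline mean step count of 5000 steps in the control group with a standard deviation of 2500 steps"). The SD of the change, or of the outcome after baseline adjustment, is not given.
- Floor's share r of the residual variance after baseline adjustment: not in the protocol. Assumed 2%, 5% or 10%.

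**3. The plan's own figure.** The protocol claims "90% power to detect a difference of 700 steps in the change in mean daily step count". At SD 2500 the standard two-sample formula needs 269 completers per arm, or 299 per arm after dropout, so the stated total of 300 is not reproduced with that SD. With 135 completers per arm, 90% power needs SD = 700 / [(1.960 + 1.282) × √(2/135)] ≈ 1774. I carry both SDs to bracket the effect of floor. Whether the sample size is adequate is a separate question.

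**4. Formulas.** Let SD be the residual SD when floor is not in the model.
- Model SE without floor: SE₀ = SD × √(2/135). This is 215.9 steps at SD 1774 and 304.3 at SD 2500.
- True SE under stratification, which is also the model SE with floor included: SE₁ = SE₀ × √(1 − r).
- Overstatement: SE₀/SE₁ = 1/√(1 − r).
- Actual alpha without floor: 2 × [1 − Φ(1.96/√(1 − r))].
- Power without floor: Φ[(700 − 1.96 × SE₀)/SE₁]. Power with floor: Φ[700/SE₁ − 1.96].

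Both powers use the same r. Stratification has already narrowed the true spread of the estimate even when floor is left out, so the fair comparator is not the power computed with no floor effect.

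**5. Results (normal approximation).**

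| r (assumed) | SE overstated by | Actual alpha | Power without → with floor, SD 1774 | Gain | Power without → with floor, SD 2500 | Gain |
|---|---|---|---|---|---|---|
| 0% | 0% | 5.0% | 90.0% → 90.0% | 0 | 63.3% → 63.3% | 0 |
| 2% | 1.0% | 4.8% | 90.2% → 90.6% | 0.3 | 63.5% → 64.2% | 0.7 |
| 5% | 2.6% | 4.4% | 90.6% → 91.4% | 0.8 | 63.7% → 65.5% | 1.9 |
| 10% | 5.4% | 3.9% | 91.2% → 92.7% | 1.6 | 64.0% → 67.9% | 3.9 |

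Gains are in percentage points, from unrounded powers. Slightly different approximations put the SD 2500 gains as low as 0.5, 1.5 and 3.6 points.

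**6. Simulation check.** Settings: 270 completers, blocks of two within floor × baseline category, 2, 6 or 10 floors, SD 1774, no true arm effect, 4000 runs per setting, participant-level ANCOVA.
- Without floor, the ratio of model SE to true SE was 0.985–1.018 at r = 0, 1.025–1.035 at r = 5% and 1.050–1.055 at r = 10%.
- With floor in the model, the ratio was 0.98–1.02 throughout, and rejection under the null was 4.3–5.7%.

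The formula and the simulation agree. The simulation uses one summary value per participant rather than the weekly or daily mixed model, whose structure the protocol does not give.

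**The case against.** **The model is not fully specified.** Section 9 names a mixed model without its random effects. A random intercept for floor would be compatible with a covariate list that covers fixed effects only, and a statistical analysis plan that is not shown could supply it. This lowers certainty about what will be run. It does not remove the point: the protocol does list its adjustment variables, the list includes one stratification factor and not the other, and nothing states that floor enters in another way.

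**Floor may add little after baseline.** This stands as a limit on size. Baseline is measured in week 1 after discharge (section 3.1), so floor differences already present then are at least partly absorbed by baseline step count. Section 2 links floors to activity in hospital, and only as something to explore. Section 1 describes the mobility protocol as being rolled out across the system over time, so a floor need not mark protocol status stably.

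**Stronger readings that the protocol does not support.**
- A reader might infer that the primary confidence interval is definitely too wide. That holds only if floor is prognostic beyond baseline, and no figure for this is given.
- A reader might infer that the omission threatens validity. It does not: the estimate is unbiased and the test errs on the conservative side.
- A reader might take the low power levels in the SD 2500 columns as raising the stakes. Those levels come from applying a baseline SD to a baseline-adjusted change outcome. They belong to the sample-size question; only the differences between columns bear on this point.

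**Conclusion.** The mismatch is real, and the direction of its effect is clear: the stated analysis does not use one of the two factors by which the trial randomises. Its size is small. With floor explaining 2–10% of the residual variance, the standard error is overstated by 1.0–5.4%, actual alpha is 4.8–3.9%, and the power lost runs from 0.3 points (2% share, SD 1774) to about 3.9 points (10% share, SD 2500). All of this rests on the assumed floor share, 135 completers per arm and a participant-level approximation to the mixed model. This is a minor point of efficiency and calibration that would rarely change a conclusion, but it is worth settling before unblinded data are seen, so that the choice of covariates is not made afterwards.

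**What to change.** In section 9, extend the primary model's adjustment set to baseline step count, time and hospital admission floor. Enter floor as a fixed effect, pooling floors that contribute few patients, or as a random intercept, and state which. Use the same model in the analysis without imputation, and include floor in the imputation model. If floor is already meant to be a random effect, saying so in section 9 resolves the primary-model part of the point.

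The cost is one phrase in the protocol and a few degrees of freedom. Floor is already recorded for randomisation, so no new data are needed.

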## 2. Overall objectives

The primary objective is to assess the effectiveness of a social incentive-based gamification intervention to increase physical activity in the 3 months after hospital discharge. We will explore patients' physical activity while in the hospital and if that differs across floors that have or have not deployed a nursing mobility protocol. We will also explore changes in patient functional decline and 30-day hospital readmission.

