## 3. Aims

### *3.1 Primary outcome*

The primary outcome variable is the change in mean daily step count from the baseline period (week 1 post-discharge) to the intervention period (weeks 2-13 post-discharge).

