### *3.2 Secondary outcome*

The secondary outcome variables are functional decline from admission to 3-months post-discharge and 30-day hospital readmission.

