## Study design

### *5.1 Design*

We will conduct a two-arm randomized, controlled trial during the 3-months after hospital discharge comparing a control group that uses a wearable device to track physical activity to an intervention group that uses the same wearable devices and receives a supportive social incentive-based gamification intervention to adhere to a step goal program. Patients will be enrolled during hospitalization from medicine and oncology floors into three phases. In phase 1 (hospitalization), patients' inpatient step counts will be monitored. In phase 2 (week 1 post-discharge), patients will have a baseline step count estimated. In phase 3 (weeks 2-13 post-discharge), patients will be randomly assigned to the control or intervention group. Patients will be considered enrolled in the trial if they complete the run-in periods (phases 1 and 2) and then are randomized into phase 3.

The enrollment phase will be part of another randomized trial (The RETAIN study) which evaluates how the magnitude of financial incentives impacts patient enrollment. This trial will be completed and unmasked to patients before they begin the phase 1 of our study.

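### Section 9 states no comparison by randomised arm for the secondary outcomes, and on the only step change the protocol defines, most of the step window falls after 30-day readmission is settled

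*Protocol*

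**What the plan says.** Protocol section 3.2 fixes the outcomes: "The secondary outcome variables are functional decline from admission to 3-months post-discharge and 30-day hospital readmission". Section 9 then gives one sentence on their analysis: "In secondary analyses, we will evaluate how differences in inpatient and changes in post-discharge step counts are associated with secondary outcome measures". The explanatory variables are step counts, inpatient and post-discharge; arm is not mentioned. The only other statement of intent is in section 2: "We will also explore changes in patient functional decline and 30-day hospital readmission". It names neither a comparison nor a model.

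The only post-discharge step change that the protocol defines is the primary outcome in section 3.1, which compares week 1 after discharge with weeks 2-13. Section 5.1 places randomisation at the start of that later period: "In phase 3 (weeks 2-13 post-discharge), patients will be randomly assigned to the control or intervention group".

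Section 9 also applies a two-sided 0.05 threshold to every hypothesis test. It reserves the word exploratory for the mobility-protocol comparison and a qualitative analysis.

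**The concern.** Two separate problems follow from the section 9 sentence.

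1. **No randomised comparison.** Sections 11.6.2 and 11.6.3 suggest that raising activity may reduce functional decline and readmission. Whether the intervention does so is answered by comparing arms. An association with step change answers a different question: patients who are sicker may both walk less and do worse, and randomisation gives no protection because the step change arises after it. This applies to both outcomes.

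2. **Timing, for readmission only.** A 30-day outcome is settled by day 30, while the step change runs to day 91. A hospital stay and the recovery after it can change recorded steps, so the outcome can partly cause the variable meant to explain it.

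At stake is what the trial can report on its two secondary outcomes. The primary analysis is not affected.

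**Working it through.** **Inputs from the protocol.** Baseline is week 1 and the intervention period is weeks 2-13 (section 3.1). Randomisation follows week 1 (sections 5.1 and 8.2). The intervention period is 12 weeks (section 9). The design has 300 patients, 150 per arm, a 700-step target, a mean of 5000 steps and 10% dropout (section 5.4).

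**Assumptions.** Day 1 is the first day after discharge, and the readmission window is days 1-30; the protocol does not state its first day. The step change in section 9 is taken to be the one in section 3.1.

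**The plan's own figure.** Weeks 2-13 are 13 - 2 + 1 = 12 weeks, which agrees with section 9. That is days 8-91, or 91 - 8 + 1 = 84 days.

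**Overlap with the readmission window.**
- Inside it: days 8-30, 30 - 8 + 1 = 23 days; 23/84 = 27%.
- After it: days 31-91, 91 - 30 = 61 days; 61/84 = 73%.
- For a patient readmitted on day t (8 to 30), the share of the step window after the event is (91 - t)/84: 99% at day 8, 85% at day 20, 73% at day 30, and 86% on average if events are uniform.
- Before randomisation: days 1-7, 7/30 = 23% of the readmission window. An event there precedes the whole intervention-period step window.

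**Which way a readmission moves the step change.** Assume, for illustration, a 5-day stay at 500 instead of 5000 steps, so 4500 steps lost per day. The stay length and the 500 are not in the protocol.
- Readmitted on days 8-30: the 84-day mean falls by 5 x 4500/84 = 268 steps/day, which is 268/700 = 38% of the target difference.
- Readmitted on days 1-7: for starts on days 1 to 7, the baseline days lost are 5, 5, 5, 4, 3, 2, 1 (mean 25/7) and the later days lost are 0, 0, 0, 1, 2, 3, 4 (mean 10/7). Baseline falls by 4500 x (25/7)/7 = 2296 and the later mean by 4500 x (10/7)/84 = 77. The change score rises by 2296 - 77 = 2219.
- Uniform over days 1-30, with all such patients randomised: (7 x 2219 - 23 x 268)/30, about +313 from unrounded values.

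The average is thus about -268 if only days 8-30 contribute and about +313 if week 1 contributes too. Sections 5.1 and 5.6 require completion of the run-in, but do not say whether a patient readmitted in week 1 can complete it.

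**Effect on a 5% test, with events on days 8-30 only.** The SD of change is not stated. The value that makes the stated 90% power hold with 150 x 0.9 = 135 per arm is 700/[(1.960 + 1.282) x sqrt(2/135)] = 1774. With 15% of 300 readmitted (45 against 255), SE = 1774 x sqrt(1/45 + 1/255) = 287. A shift of 268 is 0.93 SE, so a nominal 5% test rejects about 15% of the time with no effect of steps on readmission.

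A simulation with larger assumed losses (N = 300, SD 1774, arm effect of 700 on steps, no effect of arm or steps on readmission, 1,500 runs per scenario) gave these rejection rates for the step-association test:

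| Steps/day lost after readmission | 10% readmitted | 15% | 20% |
|---|---|---|---|
| 1000 for 4 weeks | 16% | 22% | 23% |
| 2000 for 4 weeks | 49% | 62% | 73% |
| 1000 to day 91 | 70% | 85% | 90% |
| 2000 to day 91 | 100% | 100% | 100% |

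With no loss the step test rejected in 4-5% of runs. Comparing readmission by arm rejected in 4-6% in every scenario. The negative direction in this table is built in, because no week-1 events were simulated.

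**The case against.** **The sentence does not exclude a comparison by arm, and a statistical analysis plan may contain one.** This stands. A reader might infer that the trial cannot say whether the intervention changes function or readmission. The protocol does not support that: patients are randomised, and outcome data are planned in both arms. What remains is that the protocol goes beyond silence. It states what the secondary analyses are, and the stated analysis is not by arm.

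**The associations are a legitimate interest.** Section 4 says that data are lacking on how much mobility protects patients, section 2 speaks of exploring these outcomes, and section 9 claims association, not causation. This is a good reason to keep the analyses. It does not make them the right secondary analysis of a randomised trial, and section 9 does not place them among its exploratory analyses.

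**The timing fault is narrow.** This also stands. There are two step measures and two outcomes, so four pairings, and only post-discharge change with readmission is affected. Inpatient steps precede both randomisation and readmission. For functional decline to 3 months, the step window runs alongside the outcome.

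**The window is inferred.** Section 9 does not define the step change; weeks 2-13 come from section 3.1. It is the only definition available, but the 73% depends on it.

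**The direction is not fixed.** A reader might infer that the analysis would spuriously link fewer steps to readmission. That holds only if readmissions on days 8-30 dominate; week-1 readmissions among randomised patients push the other way, and the protocol does not settle how many there would be.

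**Conclusion.** The point holds in limited form. As written, section 9 does not estimate the effect of the intervention on either secondary outcome, because the one analysis it states relates them to step counts and no section states a comparison by arm. The post-discharge step change is, in addition, a post-randomisation exposure for both outcomes.

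For 30-day readmission, 73% of the intervention-period step window follows the close of the outcome window, given the section 3.1 definition and a day 1-30 count. The association of step change with readmission therefore cannot be read as an effect of steps on readmission. The window arithmetic is firm under those two assumptions. The size and sign of the bias are not: the -268, the +313 and the simulated rejection rates rest on assumed stay lengths, step losses, readmission rates and timing.

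This should be corrected before analysis. It leaves the primary outcome untouched.

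**What to change.** Amend section 9 as follows.

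- **Secondary analyses by randomised arm, in all randomised patients.** Functional decline: a model adjusted for the baseline function score. Readmission: a risk difference or logistic regression counting events from randomisation (about day 8) to day 30, because arm cannot affect earlier events. State this time origin.
- **Step associations retained, labelled exploratory.** Define the step change used. For readmission, use only steps recorded before the event: either inpatient and week 1 steps with follow-up from day 8, or time-varying steps lagged before the event.

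The cost is protocol wording and two simple models on data already planned. Fewer readmissions are counted: days 1-7 are 23% of the 30-day window, though the loss is smaller if patients readmitted in week 1 rarely reach randomisation. The readmission comparison will also be imprecise. At an assumed 15% in each arm of 150, the 95% interval for the risk difference is about plus or minus 1.96 x sqrt(2 x 0.15 x 0.85/150) = 8 percentage points, so it should be reported as an estimate with its interval.

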## **11. Human research protection**

### *11.1 Data confidentiality*

Paper-based records will be kept in a secure location and only be accessible to personnel involved in the study. Computer-based files will only be made available to personnel involved in the study through the use of access privileges and passwords. Wherever feasible, identifiers will be removed from study-related information. Precautions are in place to ensure the data are secure by using passwords and encryption, because the research involves web-based surveys.

